### Sustainability

We define the sustainability phase as beginning after the active implementation phase is completed at each site (*i.e.*, baseline through the 3-month follow-up). At this point, the reliance on grant funds ends and sites will be encouraged to integrate Eban II into their usual services. At each site, the nine-month sustainability period will be preceded by a pre-sustainability workshop to identify and address any issues that the agencies perceive to be barriers [49]. During sustainability, Eban II will be delivered in the CBOs with trained staff serving as co-facilitators, supported by technical assistance (including quality assurance) from the management team. Technical assistance will include retraining in the intervention, sharing resources, offering suggestions on lessons learned, and review of session tapes to assess fidelity. Agencies that discontinue participation during this phase will be contacted to encourage participation and/or to identify the reasons for discontinuation. Agencies that independently deliver two eight-week cycles of the intervention with two to three couples in each cycle and maintain fidelity to the intervention core elements will be considered to have achieved sustainability. Pre-post couples-level measures will also be collected in order to examine outcomes. Sustainability will be assessed by documenting the number of couples that each agency recruited and enrolled in Eban II; the number of couples who completed the intervention; and how much technical assistance they needed and received.

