### Sample size calculation and power analyses

Sample size calculation and power analyses were conducted at both the agency- and couple-levels to ensure that we have sufficient statistical power for all analyses. At the agency level, the power analysis was based on the comparisons of key measures from providers (*e.g.*, provider attitudes toward evidence-based practices). From the 10 selected agencies, we will collect data from 100 non-clerical staff (10 providers per agency) in order to provide sufficient power to examine the within- and between-agency variation. With a type I of 0.05, type II error of 0.2 (or power of 80%), intra-agency correlation at 0.15 level, 100 raters from the 10 agencies will enable us to detect an effect size as small as 0.9 in standard deviation unit for measures from staff [65,66]. Non-parametric and parsimonious models will be used to accommodate the limitation of a relatively small number of agencies.

At the couples level, calculations were carried out based on the comparison of key outcome measures of incidents of unprotected sex and an increase in the proportion of condom use (*i.e.*, the number of times condoms were used during intercourse divided by the number of times sexual intercourse is reported) between intervention and waitlist control. With a repeated measures design, type I error 0.05, type II error 0.20, intra-couple correlation 0.4, the mean number of available repeated measures 2.5 (from baseline, post and three-month measurements), and a 2:1 ratio of intervention and waitlist control, a total of 174 couples would allow us to detect an effect size as small as 0.30 in standard deviation unit for number of unprotected sexual intercourse acts [65,67]. Thus, our planned sample of 180 couples provides sufficient power.

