#### Specific aim two

To document the implementation process and identify barriers and facilitators to adoption, fidelity, and sustainability, we will utilize a variety of analytic approaches. First, marginal distributions of each of the measures at the agency level (*e.g.*, intervention cohorts completed, provider attitudes, etc.) will be obtained. For continuous measures (*e.g.*, the number of facilitator teams trained), we will calculate the range, mean, median, quartiles, and standard deviations. For categorical measures (*e.g.*, fidelity to core elements), frequency distributions and mode will be obtained. An ordinal measure that reflects the number of intervention groups conducted at each agency will be created, which will be used to link with the number of intervention cycles completed and to test the dose–response of the intervention. For performance measures (*e.g.*, satisfaction) obtained from providers at the CBOs, analyses will be conducted, and within and between agency variations will be examined. Non-parametric methods (*e.g.*, Mann Whitney test) will be used to accommodate the relative small sample size of agencies. Rigorous statistical tests will be conducted in three steps: marginal distributions of the number of intervention cycles completed will be obtained; two-way table chi-squares or analysis of variance will be used to evaluate the relationships between the categories of number of intervention cycles completed and the extent of successful implementation, which is measured by an array of variables (*e.g.*, number of couples served, degree of fidelity, level of satisfaction with the intervention, etc.); and multivariate analyses will be conducted through regression models to examine the relationships between provider measures and number of intervention cycles completed, controlling for other agency characteristics such as agency size, number of staff, size of budget, etc.

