Data regarding acceptability, barriers, and facilitators will be derived from interviews and implementation-focused evaluation measures. As we are examining implementation in 10 large, diverse CBOs, barriers and facilitators will likely vary by agency. The qualitative data will provide the research team with extensive information about acceptability, barriers, and facilitators. In addition, we will examine the facilitator and couples’ satisfaction ratings to characterize acceptability of the intervention. These ratings will be compared both within and across agencies. Potential determinants of adoption and fidelity include but are not limited to training factors, competency at delivering the intervention, types of facilitators (*e.g.*, whether agencies used their own staff as facilitators or used the floating facilitator team), couple ‘mix’ in a given cohort, retention, and satisfaction. All of these factors will be examined when characterizing fidelity across agencies. In addition, based on interviews with facilitators and clients, we will remain open to other determinants that may emerge during implementation. There are several possible determinants of sustainability. We hypothesize that sustainability will be achieved in agencies that have their own trained staff facilitators who deliver the intervention with fidelity and who had positive experiences with the intervention during the implementation phase. To test this hypothesis, we will perform analyses in two levels: (1) Bivariate analyses between sustainability and characteristics of the CBOs and staff. The Pearson Chi-square will be used to test association. ANOVA will be used to test the means of the continuous measures (*e.g.*, ‘the number of agencies that continue to implement Eban II with fidelity’) across the different levels of a categorical measure (‘Does your agency have specific services for high-risk or HIV-positive couples? Yes/no’) at each time point of data collection; (2) Longitudinal analyses for long-term effects. Generalized linear mixed models (GLMM) [67,68] will be used to evaluate the relationship between sustainability and characteristics of the CBOs. GLMM cannot only model global fixed effects (*e.g.*, the number of full-time staff), but also can model random variation (*e.g.*, change over time of individual agency), which is particularly useful.

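### The sustainability hypothesis is to be tested with a Pearson chi-square on 10 agencies, where it can call significant some tables that Fisher's exact test puts at p = 0.07 to 0.20

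*Protocol article*

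**What the plan says.** Under *Specific aim two* of the data analysis plan, the protocol article hypothesises that sustainability will be reached in agencies whose own trained staff deliver the programme with fidelity and had good experiences with it. The first level of testing is described as "Bivariate analyses between sustainability and characteristics of the CBOs and staff", followed by "The Pearson Chi-square will be used to test association".

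Two facts fix the table size. Under *Sustainability*, agencies that meet the delivery and fidelity criteria "will be considered to have achieved sustainability", so the outcome is one yes/no value per agency. Under *Specific aim two*, the number of agencies is given: "As we are examining implementation in 10 large, diverse CBOs, barriers and facilitators will likely vary by agency". The example of an agency characteristic is itself binary: "Does your agency have specific services for high-risk or HIV-positive couples? Yes/no".

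The article does recognise that 10 is few. *Sample size calculation and power analyses* says "Non-parametric and parsimonious models will be used to accommodate the limitation of a relatively small number of agencies". *Specific aim two* says that non-parametric methods, with the Mann-Whitney test as the example, "will be used to accommodate the relative small sample size of agencies". Neither sentence names a small-sample test for contingency tables.

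**The concern.** The Pearson p-value relies on a large-sample approximation. With 10 agencies, expected counts in a two-way table are too small to trust it. The article does not leave the choice of test open. It names this one for its one stated sustainability hypothesis, while promising small-sample methods elsewhere for the same agencies.

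Determinants of sustainability are part of a primary implementation aim (aim two, item 4). A p-value that is too small could lead the authors to report a determinant, such as having own-staff facilitators, on evidence that an exact test would call weak. Several characteristics are to be screened, so this could happen more than once.

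**Working it through.** The article gives no p-value, power or error rate for this test, so there is no stated figure to reproduce.

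**Inputs**
- N = 10 agencies (*Specific aim two*).
- Binary outcome per agency (*Sustainability*).
- Binary characteristic, as in the article's own example (*Specific aim two*).
- Alpha = 0.05, two-sided. This is an assumption: the article gives 0.05 only in the power statement for staff measures ("With a type I of 0.05, type II error of 0.2 (or power of 80%), intra-agency correlation at 0.15 level") and states no level for the chi-square.
- Pearson statistic without continuity correction. The article names no correction.

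**Step 1: expected counts.** Expected count = row total x column total / 10. The smallest cell is largest when both margins are 5/5: 5 x 5 / 10 = 2.5. For any other margins it is lower.

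**Step 2: a worked table.** Suppose 5 of 5 own-staff agencies sustain and 2 of 5 others do.
- Pearson: N(ad − bc)² / (product of the four margins) = 10 x (5 x 3 − 0 x 2)² / (5 x 5 x 7 x 3) = 2250 / 525 = 4.29, p = 0.038.
- Fisher: the chance that all 3 non-sustaining agencies fall in one given group is C(5,3) / C(10,3) = 10/120 = 0.083. The opposite table is equally likely, so the two-sided p = 0.167.

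**Step 3: all 2x2 tables with N = 10 and no empty margin.** Treating tables that differ only by swapping rows, columns or axes as one pattern, 11 patterns have Pearson p ≤ 0.05. Six are also significant by Fisher (p = 0.0048 to 0.048). Five are not:

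| Table (row 1; row 2) | Pearson p | Fisher p |
|---|---|---|
| 2, 0; 1, 7 | 0.016 | 0.067 |
| 0, 4; 4, 2 | 0.035 | 0.076 |
| 1, 0; 0, 9 | 0.0016 | 0.100 |
| 0, 3; 5, 2 | 0.038 | 0.167 |
| 1, 0; 1, 8 | 0.035 | 0.200 |

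The fourth row is the table of step 2 with its axes swapped.

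**Step 4: type I error.** Unconditional size is the probability of p ≤ 0.05 when both groups share one probability of sustaining. The maximum was taken over that probability from 0.01 to 0.99.

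| Split of agencies | Pearson, maximum | Fisher, maximum |
|---|---|---|
| 1/9 | 9.0% | 0% |
| 2/8 | 8.7% | 0.7% |
| 3/7 | 6.25% | 1.6% |
| 4/6 | 5.1% | 2.1% |
| 5/5 | 6.2% | 2.1% |

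With both margins held fixed, the Pearson size reaches 16.7% (5/5 by 3/7) and 20% (1/9 by 2/8). These are the worst margins. For many others it is below 5%, for example 0.8% at 5/5 by 5/5.

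**The case against.** The strongest reply is that the damage is limited and the comparator is severe. For reasonably balanced splits the uncorrected Pearson test keeps close to 5%. Fisher's test never exceeds about 2% here, so part of the gap between the two p-values is Fisher's conservatism. A mid-p version would still call two of the five conflicting tables significant (2, 0; 1, 7: 0.0667 / 2 = 0.033; and 0, 4; 4, 2: 0.0762 − 0.0714 / 2 = 0.040). With Yates' correction none of the five is significant (p = 0.12 to 0.43). All of this stands, and it sets the size of the point. It does not rescue the test as named, since the article mentions neither correction.

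It can also be said that the small-sample wording covers these tables, or that a fallback for sparse tables belongs in a fuller plan. The first does not hold: the general promise sits beside an explicit choice of Pearson. The second would hold if the article were silent, but it names the test.

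Finally, these p-values are not the only evidence. Qualitative data and a generalized linear mixed model accompany them. That limits the consequence, but neither corrects the first-level p-values.

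**Conclusion.** The point holds, at moderate size. For a binary agency characteristic, the named test can declare significant some tables whose Fisher p lies between 0.07 and 0.20. Maximum unconditional type I error is about 5% to 6% for splits from 3/7 to 5/5 and about 9% for 1/9 and 2/8 splits. This rests on the agency as the unit, a 0.05 two-sided level and the uncorrected statistic.

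A reader might infer more than the documents support:
- That no expected count can reach 3. Only the smallest cell is capped, at 2.5. Except in the 5/5 by 5/5 table, at least one cell is 3 or more; margins 2/8 by 2/8 give one of 6.4.
- That significant results will generally be false. Six of the 11 significant patterns agree with Fisher.
- That the false-positive rate is 17% to 20%. Those are conditional worst cases for particular margins.
- That the same error is shown for the chi-squares relating cycles completed to implementation success. Those tables are not stated to be 2x2 and were not calculated. *Delivery of the Eban II intervention* requires three cycles of every agency, so that variable may hardly vary.
- That the trial's effectiveness result is at risk. Aim three uses other models on couples and is untouched.

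**What to change.** In *Specific aim two*, replace the Pearson chi-square with Fisher's exact test for 2x2 tables whose unit is the agency, and with the Fisher-Freeman-Halton test for larger ones. Apply the same rule to any two-way table earlier in that section (cycles completed against implementation success) whose unit is the agency. Do not list mid-p as interchangeable with Fisher, since the two disagree on some of these tables.

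The cost is a line or two of wording. *Trial status* reports that data cleaning and analysis had not started, so as of the article the change could be made before any result is seen. The downside is fewer nominally significant determinants, because Fisher's test has a size of at most about 2% with 10 agencies.

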### Qualitative data analysis—aims one and two

All interviews will be digitally recorded and transcribed by trained staff. ATLAS.ti will be used for qualitative analysis. Using the constant comparison analytic approach [69], a preliminary codebook will be developed both inductively and deductively from a sub-sample of interviews within and across agencies at baseline. Qualitative findings at baseline will be augmented by preliminary analyses of staff-level data from the structured measures described above (*e.g.*, burnout, attitudes toward evidence-based practices, etc.), and a baseline profile will be developed for each agency. These profiles will be used to tailor implementation at each site. This approach of using baseline data as diagnostic and informative for tailored implementation has been employed by the lead author (AH) in a prior implementation study [29]. The codebook will be elaborated upon and adjusted as each round of interviews is reviewed until thematic saturation is achieved within and across cycles of interviews. Interviews will be compared within each agency, across agencies, across different types of respondents, and over time. Additional sources of qualitative data (*i.e.* meeting minutes, archival information) will also be included in the data set. We will analyze the data specifically for barriers to and facilitators of implementation, including but not limited to the ways in which the project’s strategies and tools affect adoption, fidelity, and sustainability. In addition to identifying themes and patterns qualitatively, we will examine statistical associations between important process and outcome variables such as satisfaction with the intervention, fidelity, and retention, and improvement in behavioral outcomes. Agency profiles will be revisited and further developed at the end of the active implementation phase, and again after sustainability.

### Specific aim three

We will use repeated measures regression models and multi-level hierarchical modeling [70,71] to evaluate the effect of characteristics of agencies, staff, and couples on the behavioral and psychosocial outcomes. For repeated measures regression models, we will directly incorporate measures into models and deal with intra-class correlations from agency and staff through covariance matrix. With the multi-level nested structure from individuals, couples, agencies, and staff, the hierarchical models will be fitted in three possible steps: (a) to set the foundation for a class of hierarchical models, first we will construct individual-couple-level models with repeated measurements (baseline, post and three-month) within a couple that involves time (and intercept); (b) we will then construct across the couples-level models that involve explanatory variables such as couple demographics; health history; history of alcohol and recreational drug use; HIV/AIDS risk reduction knowledge; perceived couple sexual norms; intervention components, and a binary variable indicating immediate active treatment or wait list control; (c) we will model the regression coefficients obtained from step b at the agency level as functions of explanatory variables of agency characteristics (*e.g.*, organization size and budget, number of staff, etc.). Finally, we will then combine models from steps a, b, and c to form the complete model, which will be estimated through special procedures and software, such as WinBUGS and MlwiN [72,73].

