### Delivery of the Eban II intervention

Agencies will be activated sequentially as cohorts are completed. The flow of agency participation will be as follows: year one, two agencies; year two, two agencies; year three, three agencies; year four, three agencies. All agencies will be required to complete three Eban cycles (eight weeks/cycle). In year five, three-month follow-up evaluation data collection will continue and sustainability will be studied at the agencies that complete the active phase in year four.

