### The Eban II intervention

This eight-week, standardized, manualized intervention is facilitated by a male–female team. The intervention (see Table 2) involves: strategies that address the broad array of factors influencing risk behavior among HIV-affected couples; dyadic and group processes that take advantage of relationship and group dynamics; and educational and culturally appropriate sessions [45].

**Table 2 T2:** Core elements of the Eban II intervention

**Sessions**	**Core elements**
**Sessions**	**Principles**
1. ‘Preparing for the Journey’ (Group Session)	Gender, Ethnic, and Cultural Pride
2. ‘Enhancing Couple Communication’ (Couple session)	The Talk and Listen Technique
	Triggers to Risky Behavior
	Learn to Problem Solve with ‘FENCE’
	Identifying Sexual Abuse
3. ‘Tools for the Journey’ (Couple session)	Condom Use
4. ‘Sharing the Load’ (Couple session)	Gender, Ethnic, and Cultural Pride as Couples
5. ‘It Takes a Village’ (Group session)	Reframing Difficult Situations
6. ‘Strengthening the Village’ (Group session)	Self Talk and Relapse Prevention
7. ‘Expanding the Village’ (Group session)	Networking with others and sexual communication with partners
8. ‘Celebrating our Relationship’ (Couple session)	A review of Nguzo Saba principles of unity and rededication to protecting each other

Unlike a traditional RCT, individuals in this study will not be incentivized for attending sessions. However, our experience indicates that incentives enhance attendance and active participation; community agencies frequently provide such incentives to enhance participation in routine programs. Therefore, we will provide minimal participation incentives similar to those often provided routinely by the agencies, such as bus tokens and gift cards at pre-, post-, and three-month follow-up. In addition, usual care, services, and referrals will be available to the WL couples while they wait to enter the risk reduction program. We will learn more about the impact of incentives during sustainability, when these incentives are no longer provided.

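### The Aim three models name agency and staff as sources of correlation but leave out the Eban group, which only intervention couples share; the treatment standard error may be modestly too small.

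*Protocol article*

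**What the plan says.** All references are to the protocol article.

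- **Overview of study design; Screening and enrollment of couples.** Couples are randomised individually, 2:1, within each agency: 118 to Eban II and 62 to waitlist. Waitlist couples are offered Eban only after the three-month follow-up.
- **The Eban II intervention (Table 2).** Sessions 1, 5, 6 and 7 are group sessions; 2, 3, 4 and 8 are couple sessions. The programme is meant to work in part through "dyadic and group processes that take advantage of relationship and group dynamics".
- **Delivery of the Eban II intervention.** Each of the ten agencies runs three eight-week cycles.
- **Specific aim three.** Two model families are named. The repeated measures regression will "deal with intra-class correlations from agency and staff through covariance matrix". The hierarchical model lists individuals, couples, agencies and staff as its nested structure. Its step (b) holds the treatment indicator, and step (c) models the step (b) coefficients at agency level as functions of agency characteristics. Group, cycle and cohort appear in neither.
- **Sample size calculation and power analyses.** The only correlation in the couples-level calculation is "intra-couple correlation 0.4". On that basis "a total of 174 couples would allow us to detect an effect size as small as 0.30 in standard deviation unit".

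**The concern.** Couples who go through the same cycle at the same agency share four group sessions, the other couples in the room and the facilitators. Their outcomes may therefore be correlated beyond what the agency explains. Waitlist couples share no such group until the randomised comparison is over, so this is a partially nested design, with clustering in one arm only.

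Randomisation within agency removes agency main effects from the treatment contrast. It does not remove variation between groups, because that variation enters the Eban arm alone. A model with a common treatment effect and only an agency term counts the Eban couples as more independent than they are.

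The staff term does not reliably fill the gap. Waitlist couples have no Eban facilitator in the randomised period, so a facilitator effect is undefined for 62 of 180 couples. If one team runs several cycles, a staff term cannot tell those cycles apart.

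At stake are the width of the interval and the true false-positive rate for the primary effectiveness aim, with a smaller effect on power.

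**Working it through.** **Inputs from the article.** 118 Eban and 62 waitlist couples; 10 agencies × 3 cycles = 30 cycles; type I error 0.05 (sidedness not stated, two-sided assumed); power 0.80; effect 0.30 SD; correlation 0.4; mean of 2.5 repeated measures.

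**Assumptions.** The group ICC is not given; 0.01 to 0.10 is used, as a share of the variance of the couple's analysed outcome. Eban couples are spread evenly over the 30 cycles: m = 118/30 = 3.93.

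**The plan's own figure.** Total N for 2:1 allocation is 3 × 1.5 × f × [(1.960 + 0.842)/0.30]², where f is the variance factor.

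- Averaging over repeated measures only: f = (1 + 1.5 × 0.4)/2.5 = 0.64, giving N = 251, which is not 174.
- Applying 0.4 between the two partners as well: f = [(1 + 0.4)/2] × 0.64 = 0.448, giving N = 175.8.

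The second, an assumed reading, comes close to the stated 174. Neither contains a group term.

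**Effect of the group.**

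- Design effect in the Eban arm: D = 1 + (m − 1) × ICC.
- Variance ratio for the treatment contrast: V = (D/118 + 1/62)/(1/118 + 1/62).
- Required rise in the SE: √V − 1.
- Actual type I error: 2 × [1 − Φ(1.96/√V)].
- Couples needed: 174 × V.

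For ICC 0.05: D = 1 + 2.933 × 0.05 = 1.147; V = (0.009718 + 0.016129)/(0.008475 + 0.016129) = 1.051.

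| Assumed ICC | D | V | SE rise | Type I error | 174 becomes |
|---|---|---|---|---|---|
| 0.01 | 1.029 | 1.010 | 0.5% | 0.051 | 176 |
| 0.02 | 1.059 | 1.020 | 1.0% | 0.052 | 178 |
| 0.05 | 1.147 | 1.051 | 2.5% | 0.056 | 183 |
| 0.10 | 1.293 | 1.101 | 4.9% | 0.062 | 192 |

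**Power at 180 couples (f = 0.448).** Without grouping, 0.30/√(0.448 × 0.024604) = 2.857, and Φ(2.857 − 1.960) = 0.815. At ICC 0.10, 2.857/1.049 = 2.723, and Φ(2.723 − 1.960) = 0.777.

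**Simulation check.** 40,000 runs of 10 agencies × 3 cycles × (4 Eban + 2 waitlist couples):

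- *Agency term, common treatment effect.* Type I error 0.050, 0.053, 0.057 and 0.065 at ICC 0, 0.02, 0.05 and 0.10. At 0.10 the model SE averaged 0.157 against a true 0.167. This is slightly worse than the formula, because the ignored group variance also lowers the estimated residual variance.
- *Treatment effect varying by agency, t test on 9 degrees of freedom.* Type I error 0.049 to 0.051 at every ICC tried. Cycles are nested in agencies, so the between-agency variation in the effect absorbs the group variance.

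**The case against.** The strongest reply is step (c) of the hierarchical model. The treatment indicator is a step (b) coefficient, and step (c) models those coefficients at agency level. If that model carries a random residual on the treatment coefficient, the simulation shows the error rate holds without any group term. This stands as a limit on the point. It does not dispose of it: the article describes the coefficients only as functions of agency characteristics, mentions no residual and calls the three steps possible ones. The repeated measures regression, named separately, has no such step.

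Second, staff may include the facilitators and so pick up part of the group correlation. That is possible but partial, for the reasons given above.

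Third, the ICC is assumed, half the sessions are couple sessions, and at 0.01 to 0.02 the effect hardly matters. This stands.

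Fourth, an article may leave the exact random-effect structure to the analysis plan. But it does list the levels and sources of correlation, and the list omits the unit in which half the sessions are delivered.

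Two stronger readings are tempting. A reader might infer that the Aim three standard error is definitely too small; the documents do not support that, because they give no group ICC and leave step (c) open. A reader might also divide the minimum of 18 couples per agency by three cycles and take six per group, which gives a type I error of 0.070 at ICC 0.10. That would put the 118 Eban couples in about 20 cycles (118/6 = 19.7) instead of 30, and the article does not say so.

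**Conclusion.** The point holds in conditional form. The nesting listed for Aim three omits the Eban group, and the randomised comparison is partially nested. The treatment standard error is too small on two conditions: the group ICC is positive, and the treatment effect has no random agency-level component, as in the repeated measures model as described.

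The shortfall is modest: 0.5% to 5% of the standard error, with type I error of 0.051 to 0.062, for an assumed ICC of 0.01 to 0.10 and about 3.9 couples per group. The power loss is small too, although at ICC 0.05 the requirement of about 183 couples passes the planned 180. This is worth correcting because Aim three is the primary effectiveness aim and the change is cheap. It does not by itself undermine the trial.

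**What to change.** Either of two statements in the Aim three analysis would settle it:

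1. Add a random effect for Eban group (agency by cycle) in the intervention arm only, treating each waitlist couple as its own cluster, with small-sample degrees of freedom.
2. State that the treatment coefficient in step (c) has a random agency-level residual, and test it with small-sample degrees of freedom.

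Use the same group term when waitlist couples are analysed after crossover, since they then join groups as well. A separate facilitator-team component is not required.

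The cost of the first option is one added variance component and a slightly wider interval. The second rests on ten agencies, so its reference distribution has few degrees of freedom. No new data collection should be needed: the article plans to monitor session attendance and refers to intervention cohorts at each site, so the group identifier should be available, though this should be confirmed. Trial status says data cleaning and analysis have not begun, so the change can be fixed before results are seen.
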